### Outcome measures

The data will be collected by personnel attached to the research group who have previously been instructed in the procedures to follow and do not know the group to which the patients belong; the captures sent by the patients will be stored and classified; the evaluators will transfer the numerical values to an excel table. The images sent by the patients and the excel table are encrypted, and only the evaluators and the main researchers have access to it. This information is updated through a security cloud. All outcomes will be measured daily using WhatsApp or by email for 21 days.

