### Sampling and sample size calculation

The sampling of our research will be non-probabilistic, since we will contact the patients through social networks, and not the entire population belongs to these networks, so the selection of the sample will be possible only among those who voluntarily respond to our request.

The sample size will be calculated using the Granmo calculator v.7.12, based on the minimum clinically important differences in VASF [43], and estimating an alpha risk of 5% (0.05), a beta risk of 10% (0.10), in a unilateral contrast, a typical deviation of 12.5% (0.125), a minimum difference to detect of 10% (0.10), and a rate of follow-up losses of 15%, for which 32 subjects are required in each group, assuming that there are three groups. If the rate of loss to follow-up were observed greater than 15%, we will perform an intention-to-treat analysis. Finally, we will include 114 patients who will be divided into three groups, each group of at least 38 subjects, being able to overcome this value to assume the possible loss of follow-up.

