### Statistical analysis

The statistical analysis will be carried out through the IBM-SPSS Statistics 24 software, considering the Kolmogorov-Smirnov test as the standard normality test. We will analyze the intragroup hypothesis contrast inference by Student’s *t* test for paired variables with parametric distributions and Kruskal-Wallis *H* for non-parametric distributions. We will analyze the intragroup hypothesis contrast inference by one-factor ANOVA in the case of parametric distributions and Kruskal-Wallis *H* for non-parametric distributions. We will apply a posteriori analysis (post hoc) through Bonferroni’s contrast for parametric distributions and Mann-Whitney’s *U* for non-parametric ones. The confidence level used will be 95% (0′05), and the power of the study will be 90% (0′1). If the rate of loss to follow-up were observed greater than 15%, we will perform an intention-to-treat analysis.

A sub-analysis will be carried out, depending on the age of the patients, sex, and autonomous community of residence.

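### The between-arm test is a one-factor ANOVA or Kruskal-Wallis with no baseline term, although each outcome is measured at the start and then daily; adding baseline as a covariate is a near-free gain in precision.

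*Protocol article*

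**What the plan says.** **Data collected.** The Sample selection section has measurements taken at the start, during and at the end of the study. The Outcome measures section adds: "All outcomes will be measured daily using WhatsApp or by email for 21 days". Whether the first daily value is itself the baseline, or comes after it, is not stated.

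**Between-arm test.** The Statistical analysis section names "one-factor ANOVA in the case of parametric distributions" and Kruskal-Wallis otherwise, followed by Bonferroni or Mann-Whitney comparisons. It labels this test intragroup, the same word it uses for the paired t test just before. A one-factor ANOVA across three groups can only be the between-arm test, so the label is a slip. No covariate and no day term is named. The section does not say whether the analysed value is day 21, an average or a change from baseline. Baseline has a stated role only in the within-group paired test.

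**Other patient characteristics.** These enter only here: "A sub-analysis will be carried out, depending on the age of the patients, sex, and autonomous community of residence".

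**Sizing.** The sample size section works with "estimating an alpha risk of 5% (0.05), a beta risk of 10% (0.10), in a unilateral contrast", an SD of 0.125 and a difference of 0.10. It allows "a rate of follow-up losses of 15%, for which 32 subjects are required in each group" and then plans 114 patients, 38 per arm. The Statistical analysis section claims 90% power.

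**The concern.** With group as the only term, a one-factor ANOVA cannot use the starting value that every patient supplies. The Inclusion criteria set no window from symptom onset, and the Background puts recovery from mild illness at about two weeks, so patients may enter at different points of recovery. With 38 per arm, the baseline difference between two arms has a chance standard error of √(2/38) = 0.23 SD, against a target difference of 0.8 SD. An ANOVA on a follow-up value carries a share of that imbalance (the baseline-to-follow-up correlation times the imbalance) into the estimated effect.

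What is at stake is precision. The protocol sets 90% power beside Bonferroni comparisons that it did not size for, and baseline adjustment could recover some or all of the gap from data already planned. This is not a detail left to an analysis plan: a method is named, and it fits the planned data poorly.

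**Working it through.** **Inputs from the protocol.** Difference 0.10 and SD 0.125, so d = 0.10/0.125 = 0.8; one-sided alpha 0.05; power 90%; loss 15%; 38 enrolled per arm; three pairwise comparisons with Bonferroni.

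**Assumed.** The baseline-to-follow-up correlation r is not given; I take 0.3, 0.5 and 0.7. I assume the SD of 0.125 refers to a single follow-up value and that the SD is the same at baseline.

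**1. Reproduce the stated sample size.** n = 2(1.645 + 1.282)²/0.8² = 26.8, so 27 evaluable per arm; 27/0.85 = 31.8, so 32. This matches the protocol.

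**2. Completers at the planned enrolment.** 38 × 0.85 = 32.3, so 32 per arm.

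**3. Power without baseline, 32 per arm.** The noncentrality is 0.8 × √(32/2) = 3.2, evaluated with the noncentral t on 62 df.

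| Test | Power |
|---|---|
| One-sided 0.05 (the sizing basis) | 94% |
| Two-sided 0.05 | 88% |
| Two-sided 0.05/3 (Bonferroni; critical t 2.461) | 77% |

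The fall from 94% to 77% comes wholly from the change of significance level between sizing and analysis. If all 38 per arm complete, the Bonferroni contrast has 85%.

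**4. Power with baseline as covariate.** ANCOVA multiplies the residual variance by 1 − r², so the noncentrality becomes 3.2/√(1 − r²). A change score has variance 2(1 − r) relative to a single follow-up value. All power figures are two-sided at 0.05/3 with 32 per arm.

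| r | ANCOVA variance factor | Noncentrality | ANCOVA power | Change-score variance factor | Change-score power |
|---|---|---|---|---|---|
| none | 1 | 3.200 | 77% (follow-up value alone) | – | – |
| 0.3 | 0.91 | 3.355 | 81% | 1.40 | 60% |
| 0.5 | 0.75 | 3.695 | 89% | 1.00 | 77% |
| 0.7 | 0.51 | 4.481 | 98% | 0.60 | 95% |

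The ratio of ANCOVA to change-score variance is (1 − r²)/[2(1 − r)] = (1 + r)/2, which never exceeds 1. Below r = 0.5 the change score is worse than ignoring baseline. A three-arm pooled error (93 df) or the normal approximation raises the unadjusted and ANCOVA figures by at most about 2 points.

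**5. Size for 90% Bonferroni power (normal approximation).** Without baseline: 43 evaluable, and 43/0.85 = 50.6, so 51 enrolled per arm. With ANCOVA: 46, 38 and 26 enrolled per arm at r = 0.3, 0.5 and 0.7. At r of about 0.5 the planned 38 is roughly enough.

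**The case against.** - **The trial is adequately powered as sized.** On the sizing inputs this stands: 94% with 32 completers per arm. A reader might infer that the trial lacks power because baseline is omitted. The protocol does not support that; the gap below 90% comes from testing two-sided with Bonferroni after sizing one-sided without it. Baseline adjustment would offset the gap but did not cause it.
- **ANOVA on randomised arms is valid.** This stands. Chance imbalance costs precision and does not bias the test.
- **The analysed value is not named.** This stands too. It could be a change score or an average, in which case baseline or the daily series would be used in part. Neither choice makes a one-factor ANOVA more precise than ANCOVA of the same follow-up value or average on baseline.
- **Further harms might be inferred:** 21 repeated daily tests per outcome, or loss of every patient without a final value. The protocol proposes no day-by-day testing. Its rule for missing data is an intention-to-treat analysis above 15% loss, which is a separate matter.
- **Averaging the last seven days might seem to add a known further gain.** Its size depends on day-to-day correlations that the protocol does not give, and the reduction for an unadjusted average is not an extra reduction on top of ANCOVA. I claim no figure for it.
- **Covariates are often left to an analysis plan.** That is fair for the full covariate list, which I do not press. It does not cover a between-arm test that the protocol names.

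**Conclusion.** The point holds as a matter of efficiency: the named between-arm test is valid but leaves the collected baseline unused, or at best used through a change score. For a two-sided Bonferroni contrast at 0.8 SD with 32 completers per arm, baseline adjustment moves power from about 77% to about 81%, 89% or 98% at r = 0.3, 0.5 or 0.7. The gain therefore ranges from small to decisive, and only the trial's own correlation can settle where it falls. The figures rest on the assumed r, equal SDs, and reading the stated SD as that of a single fatigue score; they are not evidence about FEV1, PEF or walk distance. The change is worth making, but the planned analysis would not be invalid without it.

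**What to change.** 1. Make the between-arm analysis an ANCOVA of one named value, either day 21 or the mean of days 15–21, on arm and baseline value. These are different estimands, so the choice must be fixed in advance. State which measurement is the baseline.
2. A mixed model on the daily values, with baseline as covariate and the same contrast, is an acceptable alternative. Specify its covariance structure: an unstructured matrix for 21 days has 21 × 22/2 = 231 parameters, for 114 patients.
3. Keep all three pairwise comparisons (REP–NTEP, REP–SP, NTEP–SP) with Bonferroni adjustment, since the secondary objective compares REP with both other arms.
4. Correct intragroup to intergroup for this test.
5. Keep the one-factor ANOVA or Kruskal-Wallis as a sensitivity analysis.

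The cost is slightly more analysis work in the software already named, with no new data.

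### With three arms, the Bonferroni contrasts after the ANOVA are valid but more conservative than needed; Holm or a closed test would recover some power at the same nominal 5%

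*Protocol article*

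**What the plan says.** In the Protocol article, under Statistical analysis, the three groups are compared by "one-factor ANOVA in the case of parametric distributions", with Kruskal-Wallis as the non-parametric counterpart. The sentence calls this comparison intragroup. Since it is followed by post hoc pairs, I read it as the between-group comparison. The next step is "We will apply a posteriori analysis (post hoc) through Bonferroni’s contrast for parametric distributions". The non-parametric branch uses Mann-Whitney tests with no adjustment stated.

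The section does not say in words that the pairwise step requires a significant ANOVA; a posteriori suggests it. It also does not say whether the pairwise tests are one- or two-sided.

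The sample size section, which is based on VASF, works from "estimating an alpha risk of 5% (0.05"), "in a unilateral contrast", "a beta risk of 10% (0.10"), "a typical deviation of 12.5% (0.125"), "a minimum difference to detect of 10% (0.10") and "a rate of follow-up losses of 15"%. It arrives at 32 per group. The plan is then to enrol 114 patients, at least 38 per group.

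**The concern.** The secondary objective compares the respiratory programme (REP) with the toning programme (NTEP) and with sham, so the pairwise contrasts carry it. Bonferroni tests each of the three pairs at 0.05/3 = 0.0167.

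With exactly three means, the omnibus test already does most of the multiplicity work. The three pairwise nulls are linked: if any two are true, all three means are equal. Dividing alpha by three ignores this link. What is at stake is power in a trial with 38 patients per arm before losses. The validity of the tests is not in question.

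**Working it through.** **Reproducing the plan's figure.** For one unadjusted, one-sided comparison, n per arm = 2(z₀.₉₅ + z₀.₉₀)²(SD/difference)² = 2 × (1.645 + 1.282)² × (0.125/0.10)² = 26.76, rounded up to 27. Allowing for 15% losses, 27/0.85 = 31.8, rounded up to 32, which matches the stated figure. The two-sided version gives 33, or 39 with losses, and does not match. The calculation therefore makes no allowance for three pairs.

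**Evaluable numbers.** 38 × 0.85 = 32.3, so about 32 per arm are evaluable if the planned loss occurs, and 38 if nobody is lost.

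**Why 5% per pair is enough after the ANOVA.** Intersecting any two of the three pairwise nulls gives the global null. The closed family is therefore the global null plus the three pairs. Testing the global null by ANOVA at 5% and then each pair at 5% is a closed test with strong familywise control. Anything that ANOVA-gated Bonferroni rejects, this test also rejects. Holm needs no gate and rejects whatever ungated Bonferroni rejects.

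**Simulation.** 400,000 replicates per scenario; normal data, equal SDs, 1:1:1 allocation, pooled variance, two-sided pairwise t tests, standardised difference 0.10/0.125 = 0.8. The table gives power (%) for a pair that truly differs by 0.10.

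| Evaluable per arm | Pattern of means | Bonferroni, no gate | Bonferroni, ANOVA gate | Holm | Closed test |
|---|---|---|---|---|---|
| 32 | one arm 0.10 away from the other two | 77.5 | 77.5 | 80.6 | 86.0 |
| 32 | 0, 0.05, 0.10 | 77.6 | 77.2 | 78.2 | 80.5 |
| 38 | one arm 0.10 away from the other two | 85.2 | 85.2 | 87.8 | 91.8 |
| 38 | 0, 0.05, 0.10 | 85.2 | 84.9 | 85.7 | 87.4 |

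- **Closed test minus Bonferroni without the gate:** 8.5, 2.9, 6.6 and 2.2 points. With the gate: 8.5, 3.3, 6.6 and 2.5.
- **Holm minus Bonferroni without the gate:** 3.1, 0.6, 2.6 and 0.5 points.
- **Cost of the gate itself:** at most 0.4 points in these rows (77.6 − 77.2). Nearly all the loss comes from the 0.05/3 level.
- **Both programmes shown better than sham**, when both work equally, 32 per arm: Bonferroni 65.6%, Holm 71.7%, closed test 80.7%.
- **Familywise error, 32 per arm:** with all means equal, 4.3% for Bonferroni (4.2% gated) and 5.0% for the closed test. With one arm 0.10 away and the other two equal, 1.7% and 5.0%.

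**The case against.** The strongest reply is that nothing here is wrong. Bonferroni after ANOVA is conventional, valid, prespecified and comes with simultaneous intervals. That stands, and it is why the point is optional.

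Three stronger readings are tempting, and the documents do not support them:

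- **A reader might infer that the plan penalises the pairs twice.** The text never expressly makes the pairwise tests conditional on the ANOVA, and if it did, the gate would cost almost nothing.
- **A reader might infer a gain of 10 points.** That needs 27 evaluable per arm (68.7% gated against 78.8%, a gain of 10.1). From the 38 planned, this means losing 11/38 = 29%, about twice the assumed 15%.
- **A reader might take these as power figures for the respiratory objective.** The 0.8 is the VASF assumption; the protocol gives no difference or SD for FEV1 or PEF.

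It is also fair to say that Bonferroni's stricter level does buy something. Its realised familywise error is lower (1.7% against 5.0% when two arms are equal), and the extra power comes from using that unspent allowance. Both procedures stay within the nominal 5%.

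The plan has seven outcomes measured daily for 21 days, plus subgroup analyses, so loosening the one stated adjustment may look unwise. But a correction for three pairs does not address that multiplicity either.

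On timing, the article calls itself the definitive version, and its Background cites case counts from after the planned end of recruitment. That bears on how a change is documented and does not alter which rule is more efficient.

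**Conclusion.** The Bonferroni step controls error and is needlessly conservative for three arms. At the VASF design assumption and 32 to 38 evaluable patients per arm, the closed test adds about 2 to 8.5 points of power for a design-size pair and Holm about 0.5 to 3. The gain is larger for the joint claim that both programmes beat sham: at 32 per arm, 15.1 points with the closed test (80.7 − 65.6) and 6.1 with Holm (71.7 − 65.6).

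The closed-test result assumes normal data and equal variances, and its 5% applies to one outcome at one time point. The power figures also assume equal allocation and two-sided pairwise tests. The size of the gain for FEV1 or PEF cannot be derived from the protocol. The finding is a cheap improvement in efficiency, and type I control is sound as planned.

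**What to change.** In the ANOVA branch, replace Bonferroni by one of the following:

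- **Closed test:** *If the omnibus test is significant at two-sided 5%, each of the three pairs is tested at two-sided 5%; otherwise no pairwise claim is made. This controls the familywise error within one outcome and time point only.*
- **Holm:** *The three pairwise p-values are adjusted by Holm's method at two-sided 5%, within one outcome and time point only.* This suits a team that prefers not to depend on the omnibus test, and gains less.

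The closed test would also bring the ANOVA branch into line with the non-parametric branch. As written, the normality test decides whether a pair is tested at 0.05 or at 0.05/3.

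The cost is one sentence and no further patients, recorded as a dated change with a note of what data had been seen by then. The real downside is that neither procedure has matching simultaneous confidence intervals. If Bonferroni intervals are still reported, they should be labelled descriptive, because one may include zero for a pair that has been declared different.

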### Interventions

Patients will perform exclusively assigned therapeutic exercises or sedentary activities (depending on randomized allocation to the study groups) and may not combine with other physical therapy or sports physical activity. Any interference in the treatment will be grounds for exclusion, participants will be asked in the daily contacts if they have carried out any activity that can be considered as meddling in the treatment. If participants are required to combine the intervention with medications, it will be registered.

Exercise monitoring will be developed through telerehabilitation tools, that is, emerging technology through which medical rehabilitation care can be provided through a distance. Patients will be encouraged to carry out treatment and follow-up completely, through videoconferences that will encourage them to improve their health status through their personal effort and will reduce the rate of loss to follow-ups and dropouts. In the event that losses to follow-up or dropouts of more than 15% are observed, we will perform an intention-to-treat analysis.

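### The tests named for the intention-to-treat analysis take one value or one pair per patient, so as written nothing brings in patients lost before the analysed value, and their earlier daily data go unused

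*Protocol article*

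**What the plan says.** The rule on losses stands in three places. Statistical analysis has "If the rate of loss to follow-up were observed greater than 15%, we will perform an intention-to-treat analysis". Sampling and sample size calculation repeats it. Interventions words it to cover dropouts as well: "In the event that losses to follow-up or dropouts of more than 15% are observed, we will perform an intention-to-treat analysis".

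Statistical analysis then lists the tests. Within groups it names the paired t test. Its next sentence is again headed intragroup but evidently means the comparison between arms, and names "one-factor ANOVA in the case of parametric distributions and Kruskal-Wallis" for non-normal data. Post hoc contrasts are Bonferroni or Mann-Whitney. No model for repeated measurements is named.

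Outcome measures describes much richer data: "All outcomes will be measured daily using WhatsApp or by email for 21 days".

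The planned size is given in Sampling and sample size calculation: "Finally, we will include 114 patients who will be divided into three groups, each group of at least 38 subjects".

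**The concern.** Calling an analysis intention-to-treat says who belongs in it, not how a patient with incomplete data gets in. Each named test takes a single number or a before-after pair per patient and passes over anyone who lacks it. If the comparison is made at the end of the study, a patient who leaves on day 10 has some ten days of values, baseline included, and none of them counts.

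What is at stake is bias. Two arms exert themselves daily and one is sedentary, and the Blinding section concedes that patient blinding cannot be complete. Reasons for leaving could therefore differ by arm: fatigue in the exercise arms, loss of interest or recovery in the sham arm. Those who stay would then differ between arms even if the programmes did nothing, and the stated safeguard would not correct for it.

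**Working it through.** **1. The plan's own figure.** Inputs from Sampling and sample size calculation: "estimating an alpha risk of 5% (0.05), a beta risk of 10% (0.10), in a unilateral contrast", and "a typical deviation of 12.5% (0.125), a minimum difference to detect of 10% (0.10").

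- n per group = 2 × (1.645 + 1.282)² × (0.125 / 0.10)² = 2 × 8.57 × 1.5625 = 26.8, so 27 evaluable.
- With 15% losses: 27 / 0.85 = 31.8, so 32. This reproduces the plan's "a rate of follow-up losses of 15%, for which 32 subjects are required in each group".

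**2. When the rule applies.** 0.15 × 114 = 17.1. Seventeen losses (17/114 = 14.9%) do not trigger it and eighteen (18/114 = 15.8%) do. Then 114 − 18 = 96 remain, or 32 per arm if losses are even. That exceeds the 27 needed, so at the trigger the issue is bias rather than power. If the groups exceed 38, as the plan allows, the count of 18 rises.

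**3. What each named test needs.**

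| Test | Needs per patient | Uses values before loss if the analysed value is absent? |
|---|---|---|
| Paired t | one pair | No |
| One-factor ANOVA, Bonferroni contrasts | one value | No |
| Kruskal-Wallis, Mann-Whitney | one value | No |

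**4. Possible size of the bias.** The documents give no dropout mechanism, so this is a simulation under assumptions.

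- From the plan: 38 per arm; SD 12.5% of a 0–10 scale = 1.25 points; target 10% = 1 point (reading the percentages as fractions of the VASF scale).
- Assumed: visits at days 1, 7, 14 and 21; weekly correlation 0.6 to 0.8; about 20% loss per arm; probability of leaving logistic in the last observed VASF, with slopes of 1 to 1.5 in size where loss depends on fatigue.
- Two sets of runs (4000 and 3000 replicates) differed only slightly. The null rows below span both.

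| Dropout pattern | Completers' bias, no true effect | Two-sided 5% error becomes |
|---|---|---|
| Exercise patients leave when tired, sham at random | 0.10 to 0.21 points | 5.9% to 10.2% |
| Exercise patients leave when tired, sham when well | 0.18 to 0.41 points | 9.2% to 26% |

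In both rows the exercise arm looks less fatigued than it is. If loss depends on fatigue in the same way in both arms and the true effect is 1 point, completers lose only about 3% to 6% of it.

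A maximum-likelihood estimate from the values observed before loss was within 0.01 point of the truth in the null runs. Carrying the last value forward gave a bias of 0.07 to 0.35 points in the opposite direction, so that simple fill-in rule does not rescue the named tests here.

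**The case against.** A reader might infer that the analysis collapses to completers and leaves at least 18 of 114 patients unscored. The documents do not support that.

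- No section says that lost patients are dropped, and none fixes day 21 as the analysed time point.
- A fill-in rule may stand in a statistical analysis plan or full protocol that is not shown, so its absence from a journal article is not a fault. With such a rule the named tests would run on all 114.
- Eighteen is the smallest number of losses that triggers the rule. It is not a count of patients without a usable value. With daily measurement, the number unscored among those lost could be anything from none to all.

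The simulated bias is open to challenge too. The mechanisms are assumed. The largest figures need dropout in opposite directions in the two arms. Loss depended only on observed values, so the good showing of the likelihood estimate is built in. That estimate used four visits and is not a test of every mixed model one might fit. The error rates are two-sided, while the sample size rests on a one-sided contrast.

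All of this stands, and it limits the claim. What it does not remove is the choice the article does make: single-value tests for outcomes recorded daily, with a population label as the only remedy for loss. A fill-in rule would supply a number for each lost patient, but the tests would still ignore that patient's actual course.

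**Conclusion.** The concern holds in a limited form. Once losses reach 18 of 114, the plan promises an intention-to-treat analysis, but nothing in the named tests brings in a patient who lacks the analysed value. In an end-of-study comparison, the values collected before loss, baseline included, go unused. How many patients this affects cannot be computed from the documents.

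The consequence depends on why patients leave. It runs from a minor loss of effect, about 3% to 6%, if the mechanism is the same in all arms, to a bias of about 0.1 to 0.4 points, up to roughly 40% of the 1-point target, if it differs by arm under the assumptions above. These figures show what could happen and are not a forecast. The change should be made, with medium confidence in how much it will matter.

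**What to change.** Make the primary between-arm comparison a likelihood-based linear mixed model (MIXED in the SPSS version already named), in all randomised patients, whatever the loss rate.

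- **Data:** the daily or weekly values already collected.
- **Terms:** baseline, arm, day as a categorical term, and arm-by-day.
- **Covariance:** prespecified. If day 1 is baseline, three weekly values allow an unstructured matrix with 3 × 4 / 2 = 6 parameters. Twenty daily values would need 20 × 21 / 2 = 210, too many for 114 patients, so daily data call for a structured form.
- **Contrasts:** end-of-study differences between arms from this model, with the Bonferroni correction already planned.
- **Sensitivity:** one-factor ANOVA or Kruskal-Wallis on completers.

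Interventions makes interference with treatment grounds for exclusion. That sentence must be reconciled with an analysis of all randomised patients.

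The cost is revised wording and slightly more programming, with no new data or visits. The model relies on values being missing at random given what was observed, which is weaker than what a completers analysis needs but cannot be verified. With baseline as a covariate, a patient lost before any later value still adds nothing, so the number of such patients should be reported by arm.

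### Intention-to-treat applies only when losses exceed 15%, so a post-randomisation result chooses the analysis population, and the effect of exclusion for interference is undefined

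*Protocol article*

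**What the plan says.** The conditional rule appears three times in the protocol article:

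- **Statistical analysis:** "If the rate of loss to follow-up were observed greater than 15%, we will perform an intention-to-treat analysis". The section on sampling and sample size repeats this sentence.
- **Interventions:** "In the event that losses to follow-up or dropouts of more than 15% are observed, we will perform an intention-to-treat analysis". This version counts dropouts as well as losses to follow-up; the other two name only loss to follow-up.

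The Interventions section also contains a post-allocation rule: "Any interference in the treatment will be grounds for exclusion". Detection is by self-report, since "participants will be asked in the daily contacts if they have carried out any activity that can be considered as meddling in the treatment". Concomitant medication, by contrast, is only recorded.

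The article does not say:

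- which patients are analysed when losses are 15% or less;
- whether the 15% is counted overall or per arm;
- whether patients excluded for interference count towards it;
- whether exclusion ends treatment, follow-up or inclusion in the analysis.

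**The concern.** The set of patients analysed should be fixed by randomisation. Here it is fixed by a quantity observed afterwards. The 15% equals the loss allowance in the sample size calculation, but that allowance protects the number of patients. It says nothing about whether those lost resemble those kept, or whether the arms lose the same kind of patient. A low loss rate does not by itself make a completers analysis safe.

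Losses and exclusions may be related to both arm and outcome. The Background and Discussion justify the trial by the hope of preventing respiratory worsening and hospital admission. Patients who worsen may be unable to continue daily sessions, walk tests and sit-to-stand tests, so an analysis without them could leave out the patients the trial is about. Exclusion for outside activity could also differ by arm, because one arm is sedentary and two exercise.

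The undefined terms add a second problem. Someone who has seen the data could choose how to count the 15%, and so choose the population.

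**Working it through.** **Inputs from the section on sampling and sample size:** "estimating an alpha risk of 5% (0.05), a beta risk of 10% (0.10), in a unilateral contrast"; SD 0.125; difference to detect 0.10; loss allowance 15%; 32 per group required; 114 enrolled, at least 38 per group.

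**1. Reproduce the stated sample size.** n per group = 2 × (1.645 + 1.282)² × (0.125/0.10)² = 26.8, so 27. Allowing for loss, 27/0.85 = 31.8, so 32. The stated figure reproduces.

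**2. Is power the issue?** One-sided power is 90.2% with 27 per group, 94.0% with 32 and 96.7% with 38. Losing 17 of 114 leaves 97, about 32 per group. Power is adequate on the plan's own inputs; the issue is bias.

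**3. Where the trigger falls.** 0.15 × 114 = 17.1. So 17/114 = 14.9% leaves intention-to-treat off, and 18/114 = 15.8% switches it on.

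**4. Bias from differing loss between arms.** If a fraction f of an arm is lost, and those lost differ from completers by D standard deviations, the completers' mean differs from the full-arm mean by f × D × SD. For arm 1 against arm 3, each with 38 patients:

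bias = (L1 − L3)/38 × D × 0.125

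SE = 0.125 × √(1/(38 − L1) + 1/(38 − L3))

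one-sided type I error ≈ Φ(bias/SE − 1.645)

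The article gives no values for D or for the split of losses. I assume D from 0.5 to 1.0 and vary the split of 17 losses. Type I error is for the direction that the bias favours.

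| Losses (arms 1/2/3) | Bias, D = 0.5 to 1.0 | Share of 0.10 target | Type I error (nominal 0.05) |
|---|---|---|---|
| 6/6/5 | 0.002 to 0.003 | 2% to 3% | 0.056 to 0.062 |
| 10/4/3 | 0.012 to 0.023 | 12% to 23% | 0.10 to 0.18 |
| 9/8/0 | 0.015 to 0.030 | 15% to 30% | 0.12 to 0.25 |

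Example, 10/4/3 with D = 1.0: bias = 7/38 × 0.125 = 0.023; SE = 0.125 × √(1/28 + 1/35) = 0.0317; Φ(0.726 − 1.645) = 0.18.

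**5. Limiting case for 15% loss in one arm.** Suppose exactly the worst 15% of a normally distributed outcome are lost from one arm and none from its comparator. The mean shifts by φ(1.036)/0.85 = 0.274 SD, and 0.274 × 0.125 = 0.034, or 34% of the target. If 0.125 is read as 1.25 points on the 0–10 fatigue scale, this is 0.34 points. For the worst 10%, the shift is 0.195 SD (0.24 points).

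**6. Arithmetic extreme.** If the 15% is counted overall, nothing in the wording stops all 17 losses falling in one arm (17/38 = 45%). This marks the edge of the rule and is not a forecast.

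**The case against.** Four objections carry weight.

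- **A completers analysis is not stated.** A reader might infer that the plan specifies one at or below 15%. It does not; no completers or per-protocol set is named. What stands is that making intention-to-treat the response to high losses implies something else applies otherwise, and no section says what.
- **Removal from the analysis for interference is not stated.** A reader might infer it, but grounds for exclusion could mean stopping the assigned programme only. The point that holds is the ambiguity.
- **The mechanism is conjecture.** It is tempting to say that sham patients are the most likely to take up exercise. The article offers no support. Its Blinding section intends patients not to know whether they are in the sham group, while admitting that blinding is incomplete. That worsening patients stop is plausible, but it is not documented either.
- **The large figures are one-sided.** The 0.27 SD shift needs the worst patients lost from one arm with no offset in the other. Similar losses across arms largely cancel. The conversion to points assumes the 0–10 scale, and the article does not say whether the SD refers to a final value or a change.

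It may also be said that a journal article leaves analysis sets to a fuller document. That would excuse silence, but this is a stated rule, given three times. Finally, declaring everyone analysed as allocated does not recover missing values. That is correct, so the fix must include a missing-data method.

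**Conclusion.** The concern holds as a defect in a stated rule: the analysis population is decided by an observed post-randomisation loss rate, and up to 17 of 114 patients can be lost before the plan commits to intention-to-treat. The meaning of exclusion for interference, and its relation to the 15%, is unresolved.

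The rule is defective whatever the loss pattern, but the size of any bias rests on assumptions outside the article. It runs from near zero with even losses, through about 12% to 23% of the 0.10 target difference for a 10/4/3 split (lost patients 0.5 to 1.0 SD different), to about 0.27 SD if the worst 15% of one arm only are lost. The article does not support a claim that the result will be biased by any particular amount or in any particular direction. The wording should be changed before any analysis by group.

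**What to change.** **Analysis population.** In the Interventions, sample size and Statistical analysis sections, replace the 15% trigger with a statement that all randomised patients are analysed in their allocated groups as the primary analysis, whatever the loss rate. Keep the per-protocol analysis as supportive, with its set defined in advance.

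**Missing data.** State the method. Outcomes are already collected daily for 21 days, so patients who stop early contribute the values they gave. A mixed model for repeated measures is one suitable choice among several; it corrects only for loss explained by observed data. Add a sensitivity analysis for loss due to deterioration. The daily adverse-event checklist can help identify these patients, and their numbers can be reported by arm.

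**Interference.** State that it is recorded as a deviation and removes no patient from follow-up or the primary analysis. Whether such a patient continues the assigned programme is a clinical matter on which this point takes no position.

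**Cost.** No new sample size is needed. The estimate may be diluted somewhat by non-adherence, which the per-protocol analysis can help show. The analysis work grows a little, because the planned paired t tests and one-factor ANOVA or Kruskal-Wallis tests do not themselves handle missing values.
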